#### Other outcomes

Major side effects such as hypotension (systolic blood pressure below the 5th percentile for age) or apnea is tracked as is admission to ICU for airway stabilization.

The clinical outcomes are measured by trained study nurses in the ED. The research nurses also ascertain subsequent return visits/hospitalizations from the telephone follow-ups according to standardized interviewing techniques, as well as from a review of the patient health records at 72 h.

### Sample size

The sample size calculation is based on the targeted minimal significant between-group difference in proportions of hospitalizations of 10 %, which has previously been shown to impact treatment decisions. The estimated probability of hospitalization is based on our fully blinded pilot data (pilot patients form an integral part of this trial), where the overall hospitalization rate is close to 50 %. This is a superiority study in which the adoption of the Mg therapy can only be recommended for future practice if the probability of the primary outcome in the Mg group is significantly lower than in the placebo group. With 408 patients per arm (816 in total), a two-sided test with a type I error of 0.05 will have 80 % power to achieve statistical significance if Mg therapy reduces the probability of hospitalization from 50 to 40 % (that is, absolute reduction of 10 %) [82].

### Analyses

#### Primary analysis

The proportion of patients hospitalized will be compared between treatment groups using a two-sided Fisher’s exact test at the 5 % level. An intention-to-treat analysis will be used with all randomized participants included in the analysis as part of the groups to which they were randomized regardless of whether they completed the study medication or not.

#### Secondary analysis

Secondary analysis will include the following:A Fisher’s exact test to compare the rates of all cause admissions in the two arms.A repeated measures ANOVA to compare treatment arms with respect to the PRAM score, respiratory rate, heart rate, oxygen saturation, and blood pressure over time. Baseline values will be added to the model as a covariate.A Poisson model will be used to compare the number of salbutamol treatments used in the ED in the regression analysis of the two study arms, including interaction terms with the treatment group, which will be used to examine the subgroup effects with respect to the primary outcome. The following variables will be used to define subgroups: age, sex, pre-randomization PRAM score, and personal history of atopy. The statistical tests of hypotheses for the secondary outcomes a) through d) will be two-sided at the 0.00625 level to account for the issue of multiple testing and to maintain an overall type 1 error of 0.05.

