### After the intervention

Following the study medication, the patients continue to receive further salbutamol as frequently as clinically warranted as per the treating ED physician. Disposition is also determined by blinded ED physicians. Discharged patients receive a prescription for inhaled salbutamol every 4 h as necessary for the next week and daily oral corticosteroid according to local practice. All participating families receive instructions to visit their primary care provider/ED if salbutamol has to be given more often than every 4 h for increased work of breathing/severe cough and if the respiratory status interferes with usual play/normal speech or activity.

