#### Secondary outcome measures

The two groups will also be compared with respect to the following:All cause hospitalization rate by 24 h to examine Mg impact on side effects, such as hypotension necessitating admission.Changes in the PRAM, respiratory rate, and oxygen saturation from the start of the first experimental nebulization to 60, 120, 180, and 240 min and the changes in the blood pressure from the first experimental nebulization to 20, 40, 60, 120, 180, and 240 min.Number of salbutamol treatments within 240 min of starting study medication.An association between hospitalization and age, sex, symptom duration <24 h [60], pre-randomization PRAM score, personal history of atopy, and “acute viral induced wheeze” phenotype [75–81].

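### Repeated measures ANOVA, if run on complete rows, could understate a true PRAM benefit when improved children leave the ED before 240 min; a mixed model on all observed visits is the better choice

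*Protocol article*

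**What the plan says.** Protocol article, Secondary analysis: the method is "A repeated measures ANOVA to compare treatment arms with respect to the PRAM score", and also respiratory rate, heart rate, oxygen saturation and blood pressure over time. It adds that "Baseline values will be added to the model as a covariate". The estimation method, the covariance structure and the treatment of children with missing visits are not stated.

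Secondary outcome measures: the schedule is "Changes in the PRAM, respiratory rate, and oxygen saturation from the start of the first experimental nebulization to 60, 120, 180, and 240 min", and for "blood pressure from the first experimental nebulization to 20, 40, 60, 120, 180, and 240 min". Heart rate has no schedule in that section.

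Other outcomes: "The clinical outcomes are measured by trained study nurses in the ED".

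After the intervention: "Disposition is also determined by blinded ED physicians". No section requires a child to stay, or to be assessed, until 240 min.

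Sample size: in the blinded pilot data "the overall hospitalization rate is close to 50" per cent, so about half of the children are not admitted. Intention-to-treat with all randomized participants is stated under Primary analysis only.

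**The concern.** The variable under analysis probably helps to decide who is still there to be measured. The article itself says, under PRAM score, that the score is strongly associated with admission. A child whose PRAM has fallen is more likely to go home, and the later visits are then missing because of that fall. If Mg works, this happens more often in the Mg arm.

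Classical repeated measures ANOVA needs a complete row for each child. Restricted to complete rows, it would compare the slower responders of the two arms, with stronger selection in the better arm, and the estimated difference would move toward zero. At stake is the size of the PRAM effect that the trial reports, tested at the strict 0.00625 level.

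**Working it through.** **The plan's own figures.** The article gives none for this analysis. Its two related figures reproduce and do not bear on the point.
- Sample size, 50 % vs 40 %, two-sided 0.05, 80 % power: [1.960·√(2·0.45·0.55) + 0.842·√(0.5·0.5 + 0.4·0.6)]² / 0.10² gives 388 per arm, and 408 with continuity correction, as stated.
- Secondary test level: 0.05 / 8 = 0.00625, as stated.

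**Inputs from the article.** 408 per arm; PRAM at 60, 120, 180 and 240 min; entry PRAM ≥5; baseline as covariate.

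**Inputs not in the article (assumed).** PRAM variance, within-child correlation, treatment effect, and who leaves when. Three sets of assumptions were simulated. In each, a child whose observed PRAM is 3 or less may leave, and all later visits are then missing.

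- *Set A* (150 runs per scenario): true benefit 0.80 points, child-effect SD 1.3, residual SD 0.8, leaving probability 0.5 or 0.8 at 120 or 180 min.
- *Set B* (150 runs per scenario): SD 2.0, correlation 0.6, benefit 0.7 at 60 min and 1.0 afterwards on the 0 to 12 scale, leaving probability 0.3, 0.6 or 0.9 after the 60, 120 or 180 min assessment.
- *Set C* (300 runs): SDs, benefit and leaving rule of set A, but different assumed means and a baseline that shares the child effect.

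**Estimates.** Attenuation = 1 − (complete-row estimate / reference). The reference is the true benefit in sets A and C, and the full-data estimate in set B.

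| Set, leaving probability | Complete rows, placebo / Mg | Reference | Complete-row estimate | Attenuation | Mixed model, all visits |
|---|---|---|---|---|---|
| A, 0.5 | 88 / 78 % | 0.80 | 0.64 | 1 − 0.64/0.80 = 20 % | 0.80 |
| A, 0.8 | 83 / 68 % | 0.80 | 0.55 | 1 − 0.55/0.80 = 31 % | 0.80 |
| B, 0.3 | 84 / 74 % | 0.873 | 0.759 | 1 − 0.759/0.873 = 13 % | 0.880 |
| B, 0.6 | 73 / 57 % | 0.898 | 0.641 | 1 − 0.641/0.898 = 29 % | 0.913 |
| B, 0.9 | 65 / 47 % | 0.882 | 0.508 | 1 − 0.508/0.882 = 42 % | 0.904 |
| C, 0.5 | 87 / 75 % | 0.80 | 0.73 | 1 − 0.73/0.80 = 9 % | not run |
| C, 0.8 | 81 / 64 % | 0.80 | 0.67 | 1 − 0.67/0.80 = 16 % | not run |

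**Boundary cases.**
- If no child leaves before 240 min, the complete-row analysis and the mixed model agree.
- With no true effect (set B), all methods averaged between −0.007 and 0.029, so no bias appears.
- Carrying the last value forward (set B) gave 0.860, 0.871 and 0.844, a loss of 1 to 4 %. The problem therefore belongs to complete-row analysis and not to every treatment of missing visits.
- In set C the attenuation persisted when sicker children also left the ED.

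Direction was the same in every early-discharge scenario with a true effect. Only PRAM was simulated.

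**The case against.** The strongest reply is that the article never says incomplete children are dropped. The term repeated measures ANOVA is also used for mixed models fitted to all observed visits, and on that reading the problem disappears. Handling of missing visits is commonly left to the analysis plan or full protocol, neither of which is shown. This stands in part: the silence is no finding, and a reader who infers that the plan excludes children discharged early goes further than the text. What remains is that the named method has a standard complete-row reading that performs poorly in this setting.

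Early discharge is also inferred. The figure of about half not admitted refers to 24 h, not 240 min. The children still have PRAM ≥5 after initial therapy, and no discharge times are given. This stands: neither the occurrence nor the size of the loss can be shown from the article.

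The mixed model's good recovery is partly built in, because leaving was made to depend only on observed PRAM. This also stands, and it is why a sensitivity analysis is needed.

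A reader might further infer that unequal spacing of the visits invalidates the standard errors through sphericity. The documents do not support this. Sphericity concerns equal variances of pairwise differences, which unequal spacing does not by itself break. The PRAM times are equally spaced, and the comparison of arms averaged over time does not rely on sphericity. Nor does the article rank PRAM above the other secondary outcomes; all-cause hospitalization is listed first.

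**Conclusion.** The point holds as a conditional one. If the ANOVA is fitted to complete rows and improved children leave before 240 min, a true PRAM benefit could be understated, by roughly 9 to 42 % under the assumptions tried. That range is illustrative: it rests on assumed variances, effects and leaving probabilities, and it is not an estimate for this trial. For the vital signs the same reasoning applies only so far as they too are related to leaving, and this was not simulated.

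The stronger statement, that the planned analysis drops children and biases the result, is not supported. There is no bias without a true effect, so the simulations give no sign of a false claim of benefit, and the Fisher test of hospitalization on all randomized children is unaffected. The change is still worth making, because a better-suited model is available on the same data.

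**What to change.** Replace the repeated measures ANOVA with a likelihood-based mixed model for repeated measures:
- **Data:** all observed visits of all randomized children with at least one post-baseline value, analyzed in the arm to which they were randomized.
- **Fixed effects:** treatment, time, treatment × time, baseline value, and the randomization strata (site; age ≥6 years versus less).
- **Covariance:** unstructured within child. This means 4·5/2 = 10 parameters for PRAM and 6·7/2 = 21 for blood pressure, which 816 children can support.
- **Contrast:** name one for PRAM, for example the treatment difference averaged over 60 to 240 min.
- **Sensitivity analysis:** for visits missing after ED discharge or transfer, vary the assumed values of the unobserved visits by arm and report how far the conclusion holds.

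Cost: a change of wording, with the same data and standard software. The article reports 207 of 816 children enrolled as of 15 September 2015, so at that date the change could be made well before the final analysis. The small downside is that the mixed model assumes missingness depends only on observed values, which the sensitivity analysis addresses.

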### Randomization and masking

The Research Coordinating Pharmacist at SickKids produced Master Randomization tables, stratified by site and age (≥6 years versus less), using a permuted block randomization of six and eight in a 1:1 ratio of active Mg sulfate to placebo, using random number generating software. The Master Randomization tables are held at the site Research Pharmacies. Consecutively numbered kits are prepared by each pharmacy according to the step-by-step procedure manual provided by Research Coordinating Pharmacist at SickKids. Upon receiving the informed consent, the study nurse obtains the next appropriate numbered study kit from the locked research fridge in the ED (Mg has to be refrigerated) and enters the number in the confidential logbook. Since Mg sulfate solution is hypertonic, 5.5 % saline was chosen as a placebo. Using sterile water as a top-up diluent in both arms produces solutions of identical isotonicity 380 mOsm/L in both study groups. Because the deposition of inhaled drugs is weight-independent [64], a uniform Mg dose is used in all children.

The patients, research nurses and ED physicians are blinded to the treatment assignment. Only the pharmacies are unblinded. Each site is given detailed requirements for drug accountability and handling to ensure compliance with Health Canada regulations. The active Mg and placebo hypertonic saline mixture with salbutamol and sterile water are very similar in volume, color, taste, and smell when nebulized (tested in the research pharmacy at SickKids). To assess blinding, the research nurse and parents are asked at the conclusion of the experimental therapy which intervention they think the child had received.

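### Testing every secondary hypothesis at a fixed 0.00625 is valid for eight tests but gives up some power; Holm's procedure over the same eight tests holds the same error and loses no rejection

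*Protocol article*

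**What the plan says.** The Protocol article, under Primary analysis, says that "The proportion of patients hospitalized will be compared between treatment groups", "using a two-sided Fisher’s exact test at the 5 % level". Under Secondary analysis, all-cause admissions get the same kind of test, to "compare the rates of all cause admissions in the two arms". The vital signs and PRAM go into repeated-measures models, salbutamol use into a Poisson model, and subgroup effects are examined through interaction terms.

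One sentence then sets the level for all of these: "The statistical tests of hypotheses for the secondary outcomes a) through d) will be two-sided at the 0.00625 level". Its stated purpose is "to account for the issue of multiple testing and to maintain an overall type 1 error of 0.05". The article does not use the word Bonferroni, but 0.05/8 = 0.00625 exactly. It describes no step-down, ordering or dependence on the primary result.

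Under Secondary outcome measures, all-cause hospitalization is included so that an effect of magnesium on side effects leading to admission, hypotension for example, can be seen. Under Sample size, the recommendation to adopt magnesium rests on the primary outcome alone.

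**The concern.** A single fixed cut of 0.05/8 guards against the case in which all eight null hypotheses are true. Once one has been rejected, at most seven can still be true, so 0.05/7 is enough for the next, and so on. The fixed cut never uses this. The cost falls on real effects on PRAM, respiratory rate or salbutamol use whose p-values land between 0.00625 and the larger step-down limits. They go unclaimed, with no benefit to the 0.05 bound that the article sets for itself.

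All-cause hospitalization shows the effect of the cut most visibly. By definition it contains every primary event and is counted over the same 24 hours, yet it is tested at one-eighth of the primary's level.

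**Working it through.** **Inputs.** From Sample size: "With 408 patients per arm (816 in total), a two-sided test with a type I error of 0.05 will have 80 % power", for hospitalization of 50 % against 40 %. From Randomization and masking: allocation "in a 1:1 ratio of active Mg sulfate to placebo". From Primary analysis: two-sided Fisher test at 0.05. From Secondary analysis: 0.00625. Assumptions not in the document: the number of true secondary effects, their power (80 % at 0.05), their correlation (0 to 0.5), and the share of admissions for non-respiratory causes (0 to 5 percentage points, equal in both arms).

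**1. The plan's own figures.**
- Uncorrected n per arm = [1.960·√(2·0.45·0.55) + 0.842·√(0.5·0.5 + 0.4·0.6)]² / 0.10² = 387.3, so 388.
- With continuity correction: (387.3/4)·[1 + √(1 + 4/(387.3·0.10))]² = 407.1, so 408, as stated.
- Exact Fisher power at 408 per arm, by full enumeration, is 80.8 %.
- Eight tests at 0.00625: the bound is 8 × 0.00625 = 0.05. If independent, 1 − (1 − 0.00625)⁸ = 0.0489. For eight tests the rule is valid.

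**2. Why Holm loses nothing over the same eight tests.** Order the p-values and compare the j-th smallest with 0.05/(9 − j): 0.00625, 0.00714, 0.00833, 0.010, 0.0125, 0.0167, 0.025, 0.05. Stop at the first failure. Any p-value at or below 0.00625 has only smaller ones ahead of it, and every limit is at least 0.00625, so Holm reaches it and rejects it. Control at 0.05 needs no assumption about correlation.

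**3. Size of the gain.** A two-sided test with 80 % power at 0.05 has a mean statistic of 1.96 + 0.84 = 2.80. The critical value at 0.00625 is 2.73, so its power there is Φ(2.80 − 2.73), about 53 %. Simulating eight normal statistics with correlation 0 to 0.5 gives this average power over the true effects:

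| True effects among 8 | Fixed 0.00625 | Holm |
|---|---|---|
| 1 | 53 % | 53 % |
| 2 | 53 % | 54 % |
| 3 | 53 % | 55 % |
| 4 | 53 % | 56 % |
| 6 | 53 % | 59 % |
| 8 | 53 % | 63-64 % |

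Family-wise error stayed at or below 5 % throughout.

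**4. Dependence on the list.** Counting what Secondary analysis names: all-cause admission (1), PRAM, respiratory rate, heart rate, saturation and blood pressure (5), salbutamol treatments (1), and four subgroup variables (4). That is 11, or 8 if the subgroups count as one. Over 11 tests Holm starts at 0.05/11 = 0.0045. Average power is then 49 % with one or two true effects, 50-51 % with four and 52 % with six, all below the 53 % of the fixed cut. The fixed cut would keep that advantage only by exceeding its target, since 11 × 0.00625 = 0.069.

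**5. All-cause hospitalization, as context.** At 50 % against 40 %, Fisher power is 80.79 % at 0.05 and 53.61 % at 0.00625. If the events are identical, the chance of missing 0.00625 given a significant primary is 1 − 0.5361/0.8079 = 33.6 %. With 1, 2, 3 and 5 points of other-cause admissions it is 33.9, 34.5, 35.2 and 36.2 %. With a larger true effect it falls: 26 % at 50 against 39, 19 % at 50 against 38, 5 % at 50 against 35. Under Holm, the chance of passing given a significant primary is 66 % if no other secondary test is rejected, 77 % if four are, and 100 % only if all seven are.

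**The case against.** The strongest reply is that nothing here is an error. The rule is prespecified, conservative, in common use and valid for eight tests. That stands: the point concerns efficiency, not inflated error.

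It can also be said that the gain is small in realistic cases. The trial was sized only for the primary, the family includes interactions, and for blood pressure no effect is the hoped-for result. With one to four true effects the gain is 0 to 3 points. That stands too and limits the weight of the point. It does not remove it, because over the same eight tests the gain costs no rejection.

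The objection that Holm could reject less than the present rule is correct for a family longer than eight, which is why the fix must carry the list. An analysis plan that is not shown may already contain one, so the absence of a list from the article is not the complaint.

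A reader might infer something stronger: that a successful trial will contradict itself on all-cause hospitalization one time in three, so that this outcome must be tested at 0.05 straight after the primary. The documents do not support this. One in three belongs to the design effect alone. Near-complete overlap of the two outcomes is an inference from their definitions and from the Safety section's report of no hypotension or apnea so far; no all-cause rate is given. The article includes the outcome as a check on side effects, not as a second efficacy claim, and ties adoption to the primary. A p-value between 0.00625 and 0.05 against a declared stricter limit is not a contradiction.

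**Conclusion.** The point holds as a low-cost improvement. For a family of exactly eight tests, the fixed 0.00625 cut keeps type I error within 0.05 but is dominated by Holm's procedure, which gives the same guarantee and never rejects less. The benefit is 0 to 3 points of average power with one to four true effects, about 6 with six and 10 to 11 with eight, assuming each true effect has 80 % power at 0.05 and correlations lie between 0 and 0.5. The conclusion rests on the family being the eight tests that the divisor implies; for a longer family the no-loss comparison fails. The all-cause figure illustrates what the cut does at the design effect. It does not show that the plan is wrong, and Holm relieves it only to the extent that other secondary tests are also rejected.

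**What to change.** In the Secondary analysis section, replace the fixed 0.00625 level by Holm's step-down procedure at a two-sided family-wise level of 0.05 over the eight secondary tests, and name those eight in the same place. The list should say in particular whether the subgroup interactions enter as one test, as several, or outside the family. If more than eight are meant, the choice between Holm and the present rule has to be argued afresh.

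The cost is a sentence and a list, settled before unblinding, with no further patients or data. One practical price is that Holm has no simultaneous confidence intervals as simple as those matching a fixed level, so the reporting of intervals should be settled at the same time.

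Testing all-cause hospitalization in fixed sequence after a significant primary is an optional design choice, not a required correction. It would raise agreement with a significant primary to 100 % with identical events and to 97-94 % with 1 to 5 points of other admissions. It would give up a confirmatory all-cause claim when the primary fails, and it would have to keep the harm-direction assessment for which the outcome was included.

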### Safety

Magnesium blocks the neuromuscular transmission and acts as a CNS depressant. Therefore, the theoretical adverse effects with IV Mg may include a transient drop in blood pressure or apnea [83]. The potential for these problems after nebulized Mg is lower than with IV Mg because this treatment route will result in a lower systemic delivery of Mg (1/4 of the IV dose) and a lower systemic effect. Since hypotension is the only major side effect of IV Mg occurring with appreciable frequency, all patients are monitored using continuous automated blood pressure devices, and if the systolic blood pressure drops below 5^th^ percentile for age, the study will be stopped, treatment given as necessary, and the DSMC will be notified. Of note, a recent Cochrane review of 896 patients given inhaled Mg confirmed the safety of this agent [59]. No child in this study had experienced hypotension or apnea.

All adverse events are being reported to the Hospital for Sick Children Research Ethics Board according to the Hospital for Sick Children’s adverse event reporting requirements. Adverse events will be classified as mild, moderate or severe and as expected or unexpected. Expected adverse events will include cough, respiratory distress, asthma-related hospitalization, IV insertion, sinus tachycardia and bitter/salty taste of the experimental solution. Adverse reactions are managed according to the standard clinical management practices. Furthermore, we plan to document episodes of severe cough necessitating interruption of the experimental therapy for more than approximately 3 min to examine the safety profile of magnesium.

All serious, unexpected adverse drug reactions to the study medication will be reported to Health Canada within 15 calendar days, and those resulting in death or life-threatening events, within 7 calendar days. Serious adverse events include ICU admission, hypotension <5^th^ percentile for age, apnea, and any other medical event which may jeopardize the patients.

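### One multiplicity-reduced level of 0.00625 covers safety-motivated secondary outcomes (blood pressure, all-cause hospitalization) as well as efficacy, so a real harm on them is harder to declare

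*Protocol article*

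**What the plan says.** All references are to the protocol article.

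- **Level.** Secondary analysis: "The statistical tests of hypotheses for the secondary outcomes a) through d) will be two-sided at the 0.00625 level to account for the issue of"; here the sentence turns to multiplicity. The stated purpose in full is "to account for the issue of multiple testing and to maintain an overall type 1 error of 0.05". No outcome is exempted.
- **What the level covers.** Secondary outcome measures lists four items: all-cause hospitalization; changes in PRAM, respiratory rate, oxygen saturation and blood pressure; number of salbutamol treatments; and associations of hospitalization with patient characteristics. Secondary analysis puts the second item into one repeated measures ANOVA entry, "with respect to the PRAM score, respiratory rate, heart rate, oxygen saturation, and blood pressure over time". Heart rate appears there but not in the outcome list.
- **Safety purpose of blood pressure.** The second item includes "the changes in the blood pressure from the first experimental nebulization to 20, 40, 60, 120, 180, and 240 min", which adds 20 and 40 min to the times used for the other measures. The Safety section explains the attention to it: "Since hypotension is the only major side effect of IV Mg occurring with appreciable frequency".
- **Safety purpose of all-cause hospitalization.** The first item reads "All cause hospitalization rate by 24 h to examine Mg impact on side effects, such as hypotension necessitating admission".
- **Safety provisions outside the family.** Other outcomes tracks hypotension below the 5th percentile for age, apnea and ICU admission. Safety adds continuous blood-pressure monitoring, notification of the data safety and monitoring committee, and serious-adverse-event status for those events. Interim analysis has a one-sided harm test on hospitalization at 0.01 in the first 200 patients.

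**The concern.** A Bonferroni-type reduction guards against false claims of benefit when several efficacy outcomes are tested. For an outcome measured to look for harm, the costlier error is usually to miss a real difference, and a lower level makes that error more likely. The plan applies the same reduction to both kinds of outcome.

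A fall in blood pressure or a rise in all-cause admission on Mg with a p-value between 0.00625 and 0.05 would be non-significant under the stated rule. The Discussion rests much of the case for the inhaled route on its margin of safety over intravenous Mg, so these comparisons will be read closely. The concern does not depend on whether 0.00625 matches the number of tests.

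**Working it through.** **Inputs from the article.** Two-sided level 0.00625 with overall error 0.05 (Secondary analysis); 408 per arm, two-sided 0.05, 80 % power, 50 % versus 40 % (Sample size).

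**Assumptions.** The article gives no blood-pressure SD; 8 to 15 mm Hg is used as a range. A two-sample normal comparison stands in for the baseline-adjusted repeated measures model.

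**1. The plan's own figures.**
- 0.05 / 8 = 0.00625 exactly. Eight tests can be counted as all-cause admission (1), the five ANOVA measures (5), salbutamol count (1) and the subgroup item (1). The article does not list its eight tests, so this count is inferred.
- Sample size without continuity correction: [1.960 × √(2 × 0.45 × 0.55) + 0.842 × √(0.25 + 0.24)]² / 0.10² ≈ 387.3, so 388 per arm. With the correction: (387.3 / 4) × [1 + √(1 + 4 / (387.3 × 0.10))]² ≈ 407.1, so 408 per arm. Both stated figures reproduce.

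**2. Critical value.** z(1 − 0.05/2) = 1.960; z(1 − 0.00625/2) = 2.734. In the harm direction the level is 0.00625 / 2 = 0.003125.

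**3. Power lost by any effect.** New power = P(Z > 2.734 − (1.960 + z_power)).
- 80 % at 0.05: 2.734 − (1.960 + 0.842) = −0.067, power 53 %.
- 90 % at 0.05: 2.734 − (1.960 + 1.282) = −0.507, power 69 %.

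**4. Blood pressure, 408 per arm.** Standard error in SD units = √(2/408) = 0.0700.
- Detectable with 80 % power at 0.05: (1.960 + 0.842) × 0.0700 = 0.196 SD.
- At 0.00625: (2.734 + 0.842) × 0.0700 = 0.250 SD.
- Ratio 3.576 / 2.802 = 1.28. This ratio does not depend on the SD.

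| Assumed SD (mm Hg) | Detectable at 0.05 | Detectable at 0.00625 |
|---|---|---|
| 8 | 1.6 | 2.0 |
| 10 | 2.0 | 2.5 |
| 12 | 2.4 | 3.0 |
| 15 | 2.9 | 3.8 |

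Power for a given true difference:

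| True difference | At 0.05 | At 0.00625 |
|---|---|---|
| 0.15 SD | 57 % | 28 % |
| 0.20 SD | 82 % | 55 % |
| 0.25 SD | 95 % | 80 % |
| 0.30 SD | 99 % | 94 % |

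**5. All-cause hospitalization.** For 50 % versus 40 % with 408 per arm, the exact power of Fisher's test is 80.8 % at 0.05 and 53.6 % at 0.00625. By symmetry the same holds for a rise from 50 % to 60 %. This assumes an all-cause rate near the 50 % given for the primary outcome.

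**6. Alpha gained by the efficacy outcomes.** If only blood pressure left the inferred family of eight, the rest could be tested at 0.05 / 7 = 0.00714. This gain is small and is not a reason for the change.

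**The case against.** The strongest reply is that the reduced level has little bearing on how this trial judges safety. The harm of concern is hypotension as an event, not a shift in the mean. Events, apnea and ICU admission are handled outside the family, and none of the monitoring or reporting depends on the 0.00625 test. The sentence on hypotension concerns intravenous Mg; the same section calls those effects theoretical and expects less from nebulization. The stricter test still detects about a quarter of an SD, and baseline adjustment may sharpen it further. The fall from 80 % to 53 % is what any test suffers when alpha is cut this far.

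Most of this stands, and it limits the size of the point. It does not remove it. The interim test concerns hospitalization, not blood pressure. Monitoring protects the individual child but does not estimate a difference between arms. Event counts may also be too small to compare: the Safety section reports no hypotension or apnea so far, and Trial status reports 207 enrolled. If the first statement covers all 207, the approximate upper 95 % bound on the pooled rate is 3/207 = 1.4 %. The mean comparison could then be the more informative one.

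A reader might infer that the rule tilts the trial toward a finding of safety. The article does not support that. It nowhere says that a non-significant result will be taken to show safety, and the two-sided level treats benefit and harm alike.

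It may also be said that confidence intervals and reporting language belong in the analysis plan. That is fair for the detail. The level and the outcomes it covers, however, are stated in the article, so this is a stated choice and not an omission.

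**Conclusion.** The point holds in a limited form. The family at 0.00625 combines efficacy outcomes with two safety-motivated ones, blood pressure and all-cause hospitalization, and this lowers the chance of declaring a real harm on either. An effect with 80 % power at 0.05 keeps about 53 %, and the detectable mean blood-pressure difference rises by about 28 %, from 0.196 to 0.250 SD.

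The relative loss follows from the two levels alone. The mm Hg figures rest on the assumed SD and the simple two-sample approximation; the hospitalization figures rest on an assumed all-cause rate near 50 %. The practical effect is modest, because the direct harm measures and the interim harm test are outside the family. It is a cheap improvement, not a flaw that threatens the trial's conclusions.

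**What to change.** In Secondary analysis, limit the 0.00625 rule to the efficacy secondary outcomes. Report blood pressure, heart rate (if kept as a safety measure) and all-cause hospitalization as safety comparisons, each with the arm difference, an unadjusted 95 % confidence interval and a nominal p-value. State that non-significance on these is not evidence of safety. If a benefit on all-cause hospitalization is also to be claimed, that claim should stay at the adjusted level. The remaining efficacy tests can keep 0.00625, which is then conservative.

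The cost is a sentence or two of wording and more chance flags. Under no true difference, the chance of a flag in the harm direction rises from 0.3 % to 2.5 % per comparison. For three comparisons treated as independent it is 1 − 0.975³ = 7.3 %. That is acceptable where missing a harm is the worse error. The change concerns a statistical threshold only and alters no clinical rule, dose or sample size.
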